**Objectives**

General objective:

To evaluate the efficacy and safety of early convalescent plasma therapy on the progression of COVID-19.

Specific objectives:

- To study the efficacy of convalescent plasma in preventing COVID-19 clinical progression, comparing immediate plasma administration versus administration only at respiratory failure development or prolonged hospitalization.
- To study the safety of convalescent plasma in hospitalized patients with COVID-19.
- To determine the effect of convalescent plasma in the SARS-CoV-2 clearance rate in hospitalized patients with COVID-19.

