**Secondary Outcomes:**

- Clinical: days of oxygen requirement; days in mechanical ventilation; days of high-flow nasal cannula (HFNC) requirement; multiple organ dysfunction score (SOFA) (day 0, 3 and 7); days in intensive or intermediate care unit (ICU); time to respiratory failure development (Pa0_2_/FiO_2_<200 or, if arterial blood gases are not available on that day, a sustained Sa02/Fi02< 214 will be considered equivalent); length of hospitalization; 30 day-mortality.
- Microbiological: SARS-Cov2 PCR clearance in nasopharyngeal swab (days 0, 3 and 7)
- Inflammatory markers kinetics: lymphocyte count, C-reactive protein, procalcitonin, lactate dehydrogenase (LDH), D-dimer, ferritin and IL-6 evolution on days 0, 3, and 7.
- Radiologic: chest CT scan pneumonia score or portable chest X-ray progression between days 0 and 5.

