**Statistical Analysis Plan**

Continuous variables will be shown as mean and standard deviation for normally data or median and interquartile range elsewhere. Categorical variables will be shown as the number of cases and percentages

Primary outcome

We will assess the effect of early plasma compared to delayed plasma on the primary binary outcomes through chi-squared tests or Fisher’s exact test when appropriate, and odds ratios will be presented together with 95% CI and p-values. In addition, as an exploratory analysis we will adjust for age and SOFA score at enrolment, and clinically significant baseline variables if they result imbalanced between both study arms, as fixed (individual-level) effects, using logistic regression. Values of p<0.05 (2 tails) will be considered.

Secondary outcomes

We will assess the effect of early plasma compared to delayed plasma on the secondary binary variables through chi-squared tests or Fisher’s exact test when appropriate. For continuous variables with normal distribution we will use the t-test, and for continuous variables with non-normal distribution the Wilcoxon-rank-sum test or Mann-Whitney U test for comparisons. Additionally, we will analyze binary variables using logistic regression. Numerical variables will be examined using generalized linear models with log link function and gamma family function. Treatment effects, crude and adjusted, will be presented as exponentiated coefficients, i.e. odds ratios, hazard ratios or incidence rate ratios, respectively and treatment effect estimates will be presented with 95% CI.

To test difference between Kaplan-Meier estimates in survival analysis, we will use the Log-Rank test and/or Cox proportional hazard models for time-to event variables.

For the analysis of paired continuous variables, we will use Wilcoxon matched-pairs signed-rank test.

Statistical significance will be defined using a 2-sided significance level of α = .05.

Immune response subgroup analysis

A pre-planned analysis of baseline neutralizing antibodies titers and anti-SARS-CoV-2 IgG titers progression (on days 0, 3, 7), is planned for participants from the early plasma group and for the subset of participants from the deferred plasma group who will not have yet received plasma on those scheduled days. Groups will be compared through Chi-squared tests or Fisher’s exact test when appropriate.

Statistical significance will be defined using a 2-sided significance level of α = .05.

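### Every secondary and immune comparison is judged at the full two-sided 0.05, with no hierarchy, multiplicity control or exploratory label, so the chance of a false significant finding among them is well above 5%

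*Combined protocol and SAP*

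**What the plan says.** The Primary Outcomes section names a single composite. The Statistical Analysis Plan tests it by chi-squared or Fisher's test: "Values of p<0.05 (2 tails) will be considered".

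The Secondary Outcomes section lists eight clinical measures, PCR clearance, seven laboratory markers (the list ends "D-dimer, ferritin and IL-6 evolution on days 0, 3, and 7") and a radiologic outcome. The Statistical Analysis Plan closes its paragraphs on these with "Statistical significance will be defined using a 2-sided significance level of α = .05". The same sentence closes the immune response part, which is introduced as follows: "A pre-planned analysis of baseline neutralizing antibodies titers and anti-SARS-CoV-2 IgG titers progression (on days 0, 3, 7), is planned".

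The word exploratory is used once, for the covariate-adjusted primary model: "as an exploratory analysis we will adjust for age and SOFA score at enrolment".

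Secondary outcomes get a simple test and a model as well. Continuous variables have a t-test or rank-sum test, and in addition "Numerical variables will be examined using generalized linear models with log link function and gamma family function", with crude and adjusted effects to be shown. Time-to-event outcomes may have a log-rank test, a Cox model, or both. No lead analysis is named, and no covariates are listed for the adjusted secondary models.

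**The concern.** Read literally, the plan allows any secondary or immune p-value below 0.05 to be reported as statistically significant, however many are examined and whatever the primary shows. This touches a stated aim. One specific objective reads "To determine the effect of convalescent plasma in the SARS-CoV-2 clearance rate in hospitalized patients with COVID-19", and the only efficacy outcome that serves it is the secondary PCR clearance comparison.

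The trial has 58 patients and is sized for a difference of about 35 percentage points. A null primary with one or two isolated significant secondaries is therefore a realistic result, and the plan does not say how to read it. What is at stake is the standing of such findings, not the validity of the primary test.

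**Working it through.** **The plan's own figure.** The documents state no family-wise error rate. The only figure tied to alpha is the sample size, which concerns the primary alone. The usual two-proportion formula is n = [1.96·√(2p̄(1−p̄)) + 0.84·√(p₁(1−p₁)+p₂(1−p₂))]² / (p₁−p₂)². It gives 29.1 per group for 54.8% versus 20%, and 28.8 (29 after rounding up) for the rounded 35-point difference, 55% versus 20%. The stated 29 per group is reproduced, and no part of the calculation covers a secondary outcome.

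**Counting comparisons** (Secondary Outcomes; Subgroup analysis; Imaging, under Data collection and management):

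- Clinical: 8 outcomes, with SOFA at days 3 and 7, so 9.
- PCR clearance at days 3 and 7: 2.
- Markers: 7 × 2 post-baseline days = 14.
- Radiologic: 1.

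The total is 9 + 2 + 14 + 1 = 26. Immune comparisons are left out. Neutralizing capacity is measured only at enrolment, so it cannot show a plasma effect. A day 3 or day 7 difference in IgG may be antibody carried over in the transfused plasma.

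Other defensible counts:

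- One test per outcome: 8 + 1 + 7 + 1 + 2 immune = 19.
- Three CT scores and all listed immune comparisons, including day 0: 9 + 2 + 14 + 3 + 4 = 32.
- Clinical and PCR only, as a narrow subset: 9 + 2 = 11.

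**Formulas.** Take k two-sided z-tests at 0.05 with every null true, each oriented so that positive favours early plasma, with common correlation ρ through a shared normal factor F. Let a = (1.96 − √ρ·F)/√(1−ρ) and b = (−1.96 − √ρ·F)/√(1−ρ).

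- At least one rejection in either direction: 1 − E[(Φ(a) − Φ(b))^k]. At ρ = 0 this is 1 − 0.95^k.
- At least one rejection favouring plasma: 1 − E[Φ(a)^k]. At ρ = 0 this is 1 − 0.975^k.

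**Results** (either direction / favouring plasma, numerical integration over F; every ρ is an assumption):

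| k | ρ = 0 | ρ = 0.5 | ρ = 0.7 | ρ = 0.8 |
|---|---|---|---|---|
| 11 | 43.1% / 24.3% | 30.4% / 15.2% | 22.3% / 11.1% | 18.0% / 9.0% |
| 19 | 62.3% / 38.2% | 40.9% / 20.5% | 28.3% / 14.2% | 22.0% / 11.0% |
| 26 | 73.6% / 48.2% | 47.5% / 23.9% | 32.1% / 16.0% | 24.5% / 12.2% |
| 32 | 80.6% / 55.5% | 52.1% / 26.2% | 34.7% / 17.3% | 26.1% / 13.1% |

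The nominal levels for comparison are 5% and 2.5%. Expected false positives for 26 tests are 26 × 0.05 = 1.3 whatever the correlation, half of them favouring plasma.

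**Fisher's test.** At 29 per arm its actual two-sided size is about 0.009 at a 10% event rate, 0.021 at 20% and 0.025 at 30% to 50%. Of the 26 comparisons, 30-day mortality and the two clearance comparisons are plainly binary. Dropping all three as a lower bound leaves 23: 1 − 0.95²³ = 69.3% and 1 − 0.975²³ = 44.1% at ρ = 0, against 73.6% and 48.2%.

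**Several analyses of one outcome.** In 2,500 simulated null trials at 29 per arm (gamma data with shape 2, two prognostic covariates), the rank-sum test or the crude gamma model was significant in 7.8%. With the adjusted model added, it was 10.5%. A second run with Wald p-values gave 8.7% and 11.3%. The data and covariates are invented, and strictly positive data do not represent outcomes with zeros, such as ventilator days. The simulation shows the direction of the effect and is not an estimate for this trial.

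**The case against.** In the plan's favour, it already separates one powered primary from outcomes called secondary, files the immune work under subgroup analysis, and belongs to a phase II trial. Nowhere does it say that efficacy may be concluded from a secondary outcome. The analyst is to be blind to allocation, which limits deliberate selection. All of this stands, and it limits the seriousness of the point. It does not change what the significance sentence permits, and blinding does not reduce the number of tests.

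The count is also open to challenge. Marker evolution could mean one comparison per marker, and the X-ray reading only replaces CT where CT cannot be done, so it is not a further test for the same patients. That is why a range of counts is given.

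A reader might go further and infer that about 32 tests make a false efficacy claim about as likely as not. The documents do not support that, for three reasons. A total of 32 needs day-0 or IgG comparisons that cannot be read as false plasma effects. A figure near 50% needs an assumed correlation of about 0.5, and no correlation is given. It also counts rejections in either direction, and those pointing to harm cannot support an efficacy claim. Counting only those favouring plasma roughly halves the figure, to 24% for 26 tests at correlation 0.5.

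**Conclusion.** The point holds as a defect in the status given to the secondary and immune analyses. No section supplies a hierarchy, an adjustment or an exploratory label for them. For about 26 post-baseline comparisons under a global null, the chance of at least one p<0.05 is about 25% to 74% in either direction and about 12% to 48% in favour of early plasma, for common correlations from 0.8 to 0. Both the count and the correlations are assumptions. The conclusion does not turn on them: even the 11 clinical and PCR comparisons at correlation 0.8 give 18% and 9%, against nominal levels of 5% and 2.5%. The figures are approximate upper values where Fisher's test is used. Having several analyses of one outcome, none of them leading, adds looks that these counts leave out.

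Two stronger inferences fail. The error rate of the primary test is not affected, since the composite has its own 0.05 level. Nor do the documents declare the secondaries confirmatory; they simply leave their status unstated. The plan should be changed, but the point does not threaten the trial's main comparison.

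**What to change.** In the Statistical Analysis Plan:

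1. State that the unadjusted test of the composite is the only confirmatory test, at two-sided 0.05.
2. Replace the significance sentence under both the secondary and the immune headings with: *Secondary and immune-response analyses are exploratory; effect estimates with 95% CI are reported without adjustment for multiplicity, and no claim of efficacy will be based on them.* Safety need not be mentioned, because the plan sets no significance rule for it.
3. Before database lock, name one lead analysis for each secondary outcome and call the others sensitivity analyses.

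This needs no new patients, data or analyses. The cost is that the sponsor gives up claims of statistical significance on secondary and immune outcomes. The viral clearance objective would then be answered by an estimate with its interval.

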**Exclusion criteria**

(1) PaO2/Fi O2 less than 200 or need for mechanical ventilation at enrolment

(2) Coinfection with other potentially relevant respiratory pathogen on admission

(3) Pregnancy or lactation

(4) Known IgA Nephropathy or IgA deficiency

(5) Previous intravenous immunoglobulin or plasma administration within the last 60 days

(6) Previous transfusion reactions that justify plasma contraindication (e.g. severe allergy)

(7) Do not resuscitate indication

(8) Patients participating in another interventional study related to COVID-19

(9) Patients that under investigator criteria had any condition that makes them unsuitable for study participation.

* CALL score includes the following parameters: age (< or > 60 years old), lymphocyte count (< or >1000), LDH (≤ 250; 250-500; >500) and comorbidities. The following comorbidities are included in the original CALL score: hypertension, diabetes, cardiovascular disease, liver disease, asthma, chronic lung disease, HIV infection and malignancy for at least 6 months. We added to comorbidities obesity (BMI≥ 30), chronic renal failure (stage III-V), solid organ transplant (<6 months) or hematopoietic transplant (<1 year), and immunosuppressant or immunomodulators use. We specified HIV infection with CD4<200 and cancer under current systemic treatment or in advance stage (IV).

CALL score is intended to predict the risk of developing severe COVID-19 defined as: SaO2≤ 93%, tachypnea ≥30 rpm, PaO2/FiO2 ≤ 300 o mechanical ventilation. Probability of progression to respiratory insufficiency is <10% for a CALL score 4-6, 10-40% for a CALL score 7-9 and >50% for a CALL score 10-13 (PPV 15.1; NPV 0.57) [20].

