**Intervention and comparison**

The early plasma group will receive convalescent plasma on the day of enrolment. The deferred plasma group will receive convalescent plasma only if a prespecified worsening respiratory function criterion is met during hospitalization (Pa02/Fi02 <200) or, if the patient still requires hospitalization for symptomatic COVID-19 >7 days after enrolment.

The transfusion will consider a total of 400 mL of ABO compatible convalescent plasma, constituted by two 200 mL units separated by 24 hours. Plasma will be administered at a rate of 100 mL/h with close clinical monitoring. In both groups cointerventions including antibiotics, antivirals, heparin thromboprophylaxis, and immunomodulators such as steroids and tocilizumab will be allowed under the institutional protocol.

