**Subgroup analysis:**

- Immunological: IgG SARS-CoV2 titers progression (days 0, 3, 7) in participants receiving immediate plasma versus participants not receiving plasma.
- Neutralizing antibodies capacity on the day of enrolment.

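### The day-3 and day-7 IgG comparison drops deferred patients because they deteriorated, so randomisation does not protect it, and no analysis by randomised arm stands beside it

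*Combined protocol and SAP*

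**What the plan says.** The Statistical Analysis Plan, under the immune response subgroup analysis, covers baseline neutralising antibodies and the course of IgG titres on days 0, 3 and 7. On one side it "is planned for participants from the early plasma group", with no restriction on clinical course. On the other side it takes "the subset of participants from the deferred plasma group who will not have yet received plasma on those scheduled days". The Subgroup analysis section frames the IgG contrast the same way: "in participants receiving immediate plasma versus participants not receiving plasma".

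The SAP then states "Groups will be compared through Chi-squared tests", or Fisher's exact test where appropriate, at a two-sided 5% level. It describes no adjustment for this comparison, no version by randomised arm and no handling of the patients left out. The intention-to-treat statement, under Handling of missing data and dropouts, covers the primary outcome only.

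Intervention and comparison gives the deferred arm two routes to plasma. One is respiratory and allows it "only if a prespecified worsening respiratory function criterion is met during hospitalization (Pa02/Fi02 <200"). The other depends on length of stay and opens "if the patient still requires hospitalization for symptomatic COVID-19 >7 days after enrolment". The Exclusion criteria rule out "PaO2/Fi O2 less than 200 or need for mechanical ventilation at enrolment".

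**The concern.** Membership of the deferred comparator on days 3 and 7 depends on something that happens after randomisation. If the event that removes a patient is related to antibody level, the remaining deferred patients are no longer the counterpart of the early group. A difference in IgG course would then mix three things: antibody passively received with the plasma, the patients' own response, and selection by clinical course. A p-value at 0.05 on that contrast could be read as an effect of early plasma on the antibody response when part or all of it is selection.

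**Working it through.** **The plan's own figure.** The only design number in the documents is the sample size, which is not in dispute and is used here only for arm size. The pooled two-sided formula is n = [z(0.975)·√(2p̄(1−p̄)) + z(0.80)·√(p1(1−p1)+p2(1−p2))]² / (p1−p2)². With 54.8% and 20% it gives 30 per group. With 55% and 20%, matching the rounded 35-point reduction, it gives 29. Power at 29 per group for 54.8% versus 20% is 79.8%. The stated 29 per group reproduces.

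**Routes to plasma set against the sampling days.** IgG is sampled on days 0, 3 and 7 (Data collection and management), with day 0 at enrolment.

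| Deferred-arm route to plasma | Can it act by the day-3 or day-7 sample? |
|---|---|
| PaO2/FiO2 below 200 | Yes |
| Still in hospital with symptoms more than 7 days after enrolment | No, it opens after the last sample |

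PaO2/FiO2 below 200 at enrolment is an exclusion, so meeting the first route is always a post-randomisation event. Hence every per-protocol removal from the comparator on days 3 and 7 is a respiratory deterioration. The early group has no matching removal.

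**Numbers left.** The documents give no rate for the trigger. Let f be the share of the 29 deferred patients transfused by day 7 (assumption). The number remaining is 29(1−f): 26.1 at f = 0.1, 23.2 at 0.2, 17.4 at 0.4 and 14.5 at 0.5. The CALL figures in the eligibility footnote (progression 10-40% for scores 7-9, above 50% for 10-13, with entry at 9 or more) refer to a broader endpoint than PaO2/FiO2 below 200. They are context, not an estimate of f.

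**Illustration under no plasma effect.** Let q and r be seropositivity in patients who do not and do deteriorate, the same in both arms (assumptions). Early patients show (1−f)q + fr and the retained deferred patients show q, so the spurious difference (early minus deferred) is f(r−q). The rejection rates come from 20,000 simulated trials per row with 29 per arm and a two-sided chi-squared test at 0.05 without continuity correction.

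| f | q | r | Early | Deferred kept | Difference (points) | Rejected, subset | Rejected, all deferred |
|---|---|---|---|---|---|---|---|
| 0.2 | 0.8 | 0.8 | 0.80 | 0.80 | 0 | 5.0% | 4.6% |
| 0.4 | 0.8 | 0.8 | 0.80 | 0.80 | 0 | 4.9% | 4.8% |
| 0.2 | 0.8 | 0.4 | 0.72 | 0.80 | −8 | 9.9% | 4.9% |
| 0.4 | 0.8 | 0.4 | 0.64 | 0.80 | −16 | 19.8% | 4.7% |
| 0.2 | 0.4 | 0.8 | 0.48 | 0.40 | +8 | 9.0% | 4.4% |
| 0.4 | 0.4 | 0.8 | 0.56 | 0.40 | +16 | 19.3% | 4.8% |
| 0.2 | 0.9 | 0.2 | 0.76 | 0.90 | −14 | 25.3% | 4.8% |
| 0.4 | 0.9 | 0.2 | 0.62 | 0.90 | −28 | 57.3% | 4.6% |

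The last two rows assume an extreme 70-point gap. By arm, the test holds its level throughout. In the subset it holds only if serology is unrelated to deterioration, and the error can go either way. The null of no plasma effect serves only to isolate selection, since transfused plasma does carry IgG.

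**The case against.** The strongest reply concerns weight. This is a labelled subgroup analysis. Immune response is not among the three specific objectives or the primary and secondary outcomes, and the primary outcome is analysed by intention to treat. The plan states the restriction openly, and its aim is understandable: donors need IgG at 1:400 or more, so a transfused deferred patient no longer shows the response without plasma. All of this stands, and it lowers the priority. It does not make the two groups comparable.

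Several stronger readings are tempting, but the documents do not support them.

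- *A reader might infer that exactly the deteriorating patients leave and that no early patient does.* Deferred patients who worsen without reaching the threshold, or who reach it but are not yet transfused at sampling, stay in. That every early patient is kept is an inference from the lack of any restriction. The Subgroup analysis wording, by plasma received, could also drop an untransfused early patient.
- *A reader might infer that chi-squared and Fisher tests are wrong here.* The ELISA section defines seroconversion and the neutralisation section defines a positive result at 1:160, and these tests suit both. What remains is that the SAP speaks of titres without naming the binary endpoint. It plans no median split, so a loss of information from one cannot be charged to it.
- *A reader might infer that the day-0 comparisons are biased too.* If the restriction is applied day by day, almost no one is excluded at enrolment. Only a reading that requires patients to be untransfused on all scheduled days would select there as well. Testing baseline neutralising titres between randomised arms has little value but does no harm.
- *A reader might infer that a treatment-by-baseline-antibody interaction is required.* It would be very imprecise. Assume half of each arm is antibody-negative (14.5 per cell), with the whole 54.8% to 20% effect in the negatives and none in the positives. The variance of the log interaction odds ratio is 3/(14.5×0.548×0.452) + 1/(14.5×0.2×0.8) = 0.835 + 0.431 = 1.266, so the SE is about 1.13. Power is about 29%, and the 95% CI spans roughly 80-fold.

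**Conclusion.** The concern holds for the IgG comparison on days 3 and 7. Its comparator is selected on respiratory deterioration after randomisation, in one arm only, and the SAP tests the contrast at two-sided 0.05 with nothing to offset the selection. This follows from the transfusion routes, the enrolment exclusion and the sampling days, assuming plasma is given per protocol.

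The size and direction of the bias do not follow from the documents. They depend on how many deferred patients are transfused by each sampling day and on how serology relates to deterioration. The simulated rates of about 5% to about 20%, and higher under the extreme gap, show only that the effect can range from nil to material. The primary efficacy conclusion is not at risk. This should be fixed, but it does not threaten the trial.

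**What to change.** 1. Add an IgG analysis by randomised arm in all randomised patients with samples. Use log2 end-point titre on days 3 and 7 adjusted for the day-0 titre, with a stated rule for seronegative samples and for titres at the 1:6400 ceiling; or the protocol's own seroconversion endpoint by chi-squared or Fisher test; or both. Name the endpoint in the SAP.
2. Keep the comparison with untransfused deferred patients alongside it, labelled non-randomised and descriptive. Report the number excluded on each day and those patients' baseline values.
3. Optionally, report a treatment-by-baseline-antibody interaction, only as an estimate with a confidence interval.

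The cost is SAP text and a few model lines. The samples are already scheduled. The drawback is that donor IgG in deferred patients transfused before day 7 dilutes the by-arm contrast, possibly materially: at f = 0.2 to 0.4 that is about 6 to 12 of 29 patients (29×0.2 = 5.8; 29×0.4 = 11.6). The by-arm analysis therefore answers a different question, the effect of assignment to early plasma on measured IgG, and cannot replace the subset description.
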